# Room temperature stable carbetocin for the prevention of postpartum haemorrhage during the third stage of labour in women delivering vaginally: study protocol for a randomized controlled trial

**DOI:** 10.1186/s13063-016-1271-y

**Published:** 2016-03-17

**Keywords:** Postpartum haemorrhage, Room temperature stable carbetocin, Oxytocin, Non-inferiority trial

## Abstract

**Background:**

Postpartum haemorrhage (PPH) is the leading cause of maternal mortality in low-income countries and contributes to nearly a quarter of maternal deaths globally. The current available interventions for prevention of postpartum haemorrhage, oxytocin and carbetocin, are limited by their need for refrigeration to maintain potency, as the ability to maintain a cold chain across the drug distribution and storage network is inconsistent, thus restricting their use in countries with the highest burden of maternal mortality. We describe a randomized, double-blind non-inferiority trial comparing a newly developed room temperature stable formulation of carbetocin to the standard intervention (oxytocin) for the prevention of PPH after vaginal birth.

**Methods/design:**

Approximately 30,000 women delivering vaginally will be recruited across 22 centres in 10 countries. The primary objectives are to evaluate the non-inferiority of room temperature stable carbetocin (100 μg intramuscular) versus oxytocin (10 IU intramuscular) in the prevention of PPH and severe PPH after vaginal birth. The primary endpoints are blood loss ≥500 mL or the use of additional uterotonics (composite endpoint required by drug regulatory authorities) and blood loss ≥1,000 mL (WHO requirement). Non-inferiority will be assessed using a two-sided 95 % confidence interval for the relative risk of the above endpoints for room temperature stable carbetocin versus oxytocin. The upper limit of the two-sided 95 % confidence interval for the relative risk for the composite endpoint of blood loss ≥500 mL or the use of additional uterotonics, and for the endpoint of blood loss ≥1,000 mL, will be compared to a non-inferiority margin of 1.16 and 1.23, respectively. If the upper limit is below the corresponding margin, non-inferiority will have been demonstrated. The safety analysis will include all women receiving treatment. Safety and tolerability will be assessed by a review of adverse events, by conducting inferential testing with significance levels for between-group comparisons.

**Discussion:**

If the results of the study show that room temperature stable carbetocin is a safe and effective alternative to oxytocin, this could have a substantial impact on the prevention of postpartum haemorrhage and maternal survival worldwide.

**Trial registration:**

ACTRN12614000870651 (14 August 2014)

**Electronic supplementary material:**

The online version of this article (doi:10.1186/s13063-016-1271-y) contains supplementary material, which is available to authorized users.

## Background

Postpartum haemorrhage (PPH) is defined as a blood loss of ≥500 mL within 24 hours of delivery, while severe PPH (sPPH) is defined as a blood loss of ≥1,000 mL within the same time frame [1]. PPH is the leading cause of maternal mortality in low-income countries, contributing to nearly a quarter of maternal deaths globally. In addition, PPH is a significant contributor to severe maternal morbidity and long-term disability, as well as to a number of other severe maternal conditions generally associated with more substantial blood loss, including shock and organ dysfunction [2–4]. Improving health care for women during childbirth in order to prevent and treat PPH is an essential step towards the achievement of the United Nations Millennium Development Goals.

The majority of deaths due to PPH could be avoided through the use of prophylactic uterotonics during the third stage of labour and by timely and appropriate management. Injectable oxytocin has been recommended by the World Health Organization (WHO) for routine use during the third stage of labour and is the preferred drug for the prevention and management of blood loss after childbirth; however, several studies have demonstrated that oxytocin loses potency in field conditions, particularly in tropical climates [1, 5, 6]. To decrease potency loss due to degradation, oxytocin must be either stored at controlled room temperature (25 °C or lower) for a restricted amount of time or refrigerated (2 °C to 8 °C), making its use difficult in low resource settings. To ease this barrier, several groups have been researching heat stable oxytocin formulations [5]. Though some progress has been made in this area, there is currently no heat stable oxytocin formulation for therapeutic use [7].

Carbetocin (1-deamino-1-monocarba-(2-O-methyltyrosine)-oxytocin) is a long-acting synthetic agonist analogue of the human oxytocin, and it appears to be a promising agent in the prevention of PPH following vaginal delivery. The clinical and pharmacological properties of carbetocin are similar to those of oxytocin. However, carbetocin is a more stable molecule and induces a prolonged uterine response, when administered postpartum, in terms of both amplitude and frequency of contractions due to its longer half-life [8–10]. In a Cochrane systematic review including 11 studies (2,635 women), the use of carbetocin resulted in a statistically significant reduction in the use of additional/therapeutic uterotonics compared to oxytocin for those who underwent caesarean delivery (risk ratio (RR) 0.62; 95 % confidence interval (CI) 0.44 to 0.88; four trials, 1,173 women), but not for vaginal delivery. Compared to oxytocin, carbetocin was associated with reduced uterine massage following both caesarean delivery (RR 0.54; 95 % CI 0.37 to 0.79; two trials, 739 women) and vaginal delivery (RR 0.70; 95 % CI 0.51 to 0.94; one trial, 160 women). There were no statistically significant differences between carbetocin and oxytocin in terms of risk of any PPH or in risk of sPPH [11].

Carbetocin is currently approved in multiple countries for the prevention of PPH during caesarean section. The drug is licensed to be administered by slow intravenous (IV) single injection at a dose of 100 μg. Its current formulation requires refrigeration.

A room temperature stable (RTS) variant of carbetocin has recently been developed and is now approved in the European Union; this variant differs from the current carbetocin formulation only in its excipients (Table 1). The stability data from long-term studies performed at 30 °C and 75 % relative humidity, as well as accelerated at 40 °C and 75 % relative humidity, indicate a shelf life of at least 36 months at 30 °C for the new RTS formulation of carbetocin. Carbetocin RTS therefore represents a promising intervention for reducing PPH, particularly in settings where cold storage is difficult to achieve and maintain. Here, we describe a planned randomized trial to evaluate the non-inferiority of carbetocin RTS versus oxytocin after vaginal delivery in the prevention of PPH and sPPH.

**Table 1 Tab1:** Composition of carbetocin RTS and carbetocin

New carbetocin RTS formulation			Current carbetocin refrigerated formulation (Duratocin®, Ferring)^a^		
Component	Amount (mg/mL)	Function	Component	Amount (mg/mL	Function
Carbetocin	0.100	Active substance	Carbetocin	0.100	Active substance
Succinic acid	1.19	Buffer	Sodium chloride	9	Isotonicity agent
Mannitol	47.0	Isotonicity agent	Glacial acetic acid	to pH 3.8	pH adjustment
L-methionine	1.00	Antioxidant	Water for injection	1.0 mL	Solvent
Sodium hydroxide 2 N	to pH 5.45	pH adjustment	--	--	--
Water for injection	1.0 mL	Solvent	--	--	--

^a^Carbetocin 100 μg/mL was first approved in Canada in June 1997 and is currently registered in more than 70 countries under the trade names PABAL/DURATOCIN/LONACTENE/DURATOBAL

*RTS* room temperature stable

## Methods/design

### Primary objectives and hypotheses

The trial has two primary objectives: 1) To evaluate non-inferiority of carbetocin RTS versus oxytocin after vaginal delivery in the prevention of the composite endpoint “blood loss of 500 mL or more or the use of additional uterotonics” at one hour and up to two hours for women who continue to bleed after one hour; and 2) to evaluate non-inferiority of carbetocin RTS versus oxytocin in the prevention of sPPH (≥1,000 mL blood loss) at one hour and up to two hours for women who continue to bleed after one hour.

For both objectives the hypotheses are: 1) carbetocin RTS is non-inferior to oxytocin in terms of the proportion of women with blood loss ≥500 mL or the use of additional uterotonic drugs after vaginal delivery within a non-inferiority margin of 1.16 on the relative risk scale, and the proportion of women with blood loss ≥1,000 mL after vaginal delivery within a non-inferiority margin of 1.23 on the relative risk scale; and 2) carbetocin RTS is superior to oxytocin in terms of the proportion of women with blood loss ≥500 mL or use of additional uterotonic drugs, and in terms of the proportion of women with blood loss ≥1,000 mL after vaginal delivery. For each of the two primary endpoints, superiority will be tested if non-inferiority has been demonstrated.

Investigators and other assessors will be blinded to individual treatment allocation. The study will be conducted by the HRP/WHO, and WHO staff will also remain blinded to individual participant treatment allocation during the conduct of the trial.

### Study drug

Carbetocin RTS (Ferring, St. Prex, Switzerland) will be administered as a single IM dose of 100 μg in a 1 mL solution. Oxytocin 10 IU/mL (Syntocinon®, Novartis, Basel, Switzerland) will be administered as a single intramuscular (IM) dose in a 1 mL solution. In order to maintain the blindness of the trial, carbetocin RTS and oxytocin will be provided in 1 mL ampoules in consecutively numbered treatment packs arranged in dispensers and will be stored in a refrigerator at 2 °C to 8 °C.

### Study design

This clinical trial will be conducted in compliance with the clinical trial protocol, good clinical practice and the applicable regulatory requirements. The trial is planned to be conducted at 22 centres in 10 countries: Argentina, Egypt, India, Kenya, Nigeria, Singapore, South Africa, Thailand, Uganda and the United Kingdom. Approximately 30,000 women will be included in the trial. The recruitment period will be approximately 12 months in each country.

The care provider in charge of antenatal care visits at the hospital will inform potentially eligible pregnant women (women with no allergies to carbetocin, other oxytocin homologues or excipients, or serious cardiovascular disorders) about the trial.

At admission for labour at the hospital, the woman will be approached for participation in the trial when she is in early labour and if her vital signs are normal, and she is not stressed. The investigator will invite her to sign the informed consent. Informed consent will be obtained before any trial-related procedures are carried out.

During the second stage of labour when vaginal delivery is imminent, the woman will be randomized to receive either a single dose of oxytocin 10 IU IM or a single dose of carbetocin RTS 100 μg IM.

The investigator will administer the investigational medicinal product (IMP) immediately after the birth of the baby (preferably within one minute). Once the IMP has been administered, the investigator will follow the management of the third stage of labour as recommended in WHO guidelines and as detailed in the trial’s manual of operations.

Once the cord is clamped (1–3 minutes after delivery of the baby) and cut, the investigator will place a calibrated drape under the woman’s buttocks and blood loss will be measured for one hour or two hours postpartum if the bleeding continues beyond one hour (blood loss measuring details are provided in the trial’s manual of operations).

The woman will end her participation in the trial after her discharge or if she is transferred to a higher care unit, such as an intensive care unit (ICU). Data will be entered into a validated online database system compliant with the FDA 21 CFR part 11.

The trial master protocol was approved by the World Health Organization Research Ethics Review Committee. All sites received ethics approval from their institutional/national boards (see additional file 1 for the list of ethics committees that reviewed and approved the proposal).

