### Primary and secondary endpoints

The primary and secondary endpoints are listed in Table 2. The trial is being conducted as an effectiveness trial with the objective of carbetocin RTS being registered for the indication “prevention of postpartum haemorrhage” by drug regulatory authorities if it is shown to be non-inferior or superior to oxytocin. The primary composite endpoint is blood loss ≥500 mL or use of additional uterotonics. For the purpose of evaluating clinical effectiveness and for the potential inclusion of carbetocin RTS in future WHO guidelines and the Model List of Essential Medicines, the more substantive endpoint of blood loss ≥1,000 mL is also a primary endpoint. Since the two primary endpoints serve independent objectives, there will be no adjustment for the type I error rate for multiplicity of endpoints.

**Table 2 Tab2:** Primary and secondary endpoints

Primary endpoints
The proportion of women: • with blood loss of 500 mL or more or the use of additional uterotonics at one hour and up to two hours for women who continue to bleed after one hour; • with blood loss of 1,000 mL or more at one hour and up to two hours for women who continue to bleed after one hour.
Secondary endpoints
The proportion of women: • with blood loss of 500 mL or more at one hour (or two hours postpartum if the bleeding continues beyond one hour); • receiving additional uterotonics at one hour (or two hours postpartum if the bleeding continues beyond one hour); • receiving additional uterotonics up to time of discharge; • receiving blood transfusion up to time of discharge; • with manual removal of placenta up to time of discharge; • having additional surgical procedures (for example, suturing of cervix/high vaginal tear, exploration of uterine cavity under general anaesthetic, uterine compression suture, uterine or hypogastric ligation, hysterectomy) up to time of discharge; • with maternal death; • with composite outcome of maternal death or severe morbidity (admission to intensive care unit, hysterectomy, blood loss of two litres or more, uterine inversion) up to time of discharge Blood loss in mL at one hour (or two hours postpartum if the bleeding continues beyond one hour). The incidence and severity of adverse or serious adverse events up to the time of discharge. Newborn outcomes (vital status, Apgar score at 5 minutes, resuscitation of the baby, mechanical ventilation).

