### Assessment of safety

Comprehensive assessment of the safety of the study drugs will be performed throughout the course of the trial, from the time of the participant’s signature of informed consent until discharge. Trial centre personnel will report any adverse event (AE), whether observed by the investigator or reported by the participant.

The intensity of an AE will be classified using a three-point scale: mild ─ awareness of signs or symptoms, but no disruption of usual activity; moderate ─ event sufficient to affect usual activity; and severe ─ inability to work or perform usual activities. AEs will also be classified as possibly related to study drug (that is, there is evidence or argument to suggest a causal relationship between the AE and the study drug), or not related to study drug (that is, there is no reasonable evidence or argument to suggest a causal relationship between the AE and the study drug).

The outcome of an AE will be classified as: recovered/resolved (fully recovered or the condition has returned to the level observed at initiation of trial treatment); recovered/resolved with sequelae (resulted in persistent or significant disability/incapacity); recovering/resolving; not recovered/not resolved; or fatal.

An AE will be considered serious if it results in death, is life-threatening, requires in-patient hospitalization or prolongation of existing hospitalization, results in persistent or significant disability/incapacity, is a congenital anomaly/birth defect, or is an important medical event. If an investigator becomes aware of a serious AE after the participant’s hospital discharge, and he/she assesses the serious AE to have a reasonable possible causality to the study drug, the case will be reported, regardless of how long after the end of the trial the AE took place.

Since the amount of blood lost is collected as an efficacy endpoint, only the following blood loss events that fulfil the criteria for a serious AE will be recorded: ICU admission (adult ICU admission, not maternity/labour ward high care); surgical intervention for control of haemorrhage (hypogastric artery ligation or uterine compression sutures); peripartum hysterectomy, blood loss ≥ 2,000 mL; and uterine inversion.

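### Participation ends at transfer to a higher care unit, although most secondary endpoints and all safety data are defined to discharge; the two rules must be reconciled

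*Protocol article*

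**What the plan says.** The Study design section closes the participant's path with "The woman will end her participation in the trial after her discharge or if she is transferred to a higher care unit", and gives the ICU as an example of such a unit.

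Table 2 (Primary and secondary endpoints) sets other end points for data collection:

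- Transfusion: "receiving blood transfusion up to time of discharge". Later additional uterotonics and manual removal of placenta have the same limit.
- Surgery: the list ends "uterine compression suture, uterine or hypogastric ligation, hysterectomy) up to time of discharge".
- The composite: "with composite outcome of maternal death or severe morbidity (admission to intensive care unit, hysterectomy, blood loss of two litres or more, uterine inversion", again to discharge.
- Adverse events: "The incidence and severity of adverse or serious adverse events up to the time of discharge".
- Death as an endpoint of its own: "with maternal death", with no window.

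Assessment of safety covers the period from "signature of informed consent until discharge". Among the bleeding-related events to be recorded as serious adverse events it lists "ICU admission (adult ICU admission, not maternity/labour ward high care", together with surgery to control haemorrhage, hysterectomy, blood loss of 2,000 mL or more and uterine inversion.

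**The concern.** Transfer to a higher care unit happens after randomization and is largely a consequence of what the trial measures: heavy bleeding and its complications. A rule that ends participation there would stop observation in the women most likely to be transfused, operated on or to die. Transfer is not a reason for exclusion from the modified ITT population, so these women would stay in the denominator while their later events went unrecorded.

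The endpoints at stake are not minor. The Discussion names transfusion and maternal death as the two outcomes rated critical, alongside blood loss of 1,000 mL or more, in the earlier WHO recommendations. The DSMC's reviews at 5,000 and 15,000 women would rest on the same data. Sites that follow different sections of the protocol would also collect different data.

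**Working it through.** **1. The plan's own figure.** Inputs from Sample size calculation: severe PPH 2% in both arms, margin 0.46%, power 80%, one-sided 2.5%; allocation 1:1 from Randomization.

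n per arm = (1.96 + 0.8416)² × 2 × 0.02 × 0.98 / 0.0046² = 14,541, so 29,082 in total, as stated. Allowing for 3% loss: 29,082 / 0.97 = 29,982, given as 30,000. These inputs concern blood loss at one to two hours. Nothing that happens after that window enters the calculation.

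**2. The rules side by side, for a woman transferred before discharge.**

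| Item | Window stated | If participation ends at transfer |
|---|---|---|
| Primary endpoints | 1 hour, up to 2 if bleeding continues | Complete, unless transfer falls inside the window |
| Later uterotonics, transfusion, manual removal, surgery | Discharge | Events after transfer not collected |
| Death or severe morbidity (composite) | Discharge | ICU transfer already counts as an event; other higher care units do not |
| Maternal death alone | None stated | Deaths after transfer not collected |
| Adverse events and their outcome | Discharge | Later events, and the outcome of the event that led to transfer, not collected |

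The article states no route for collecting outcomes between transfer and discharge. The one late route is in Assessment of safety: a serious adverse event that the investigator happens to learn of after hospital discharge and judges possibly caused by the drug. That is selective and does not cover the gap.

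For the composite, a woman moved first to a higher care unit that is not an ICU is not protected. The safety section excludes maternity or labour ward high care from ICU admission, and a later ICU admission, hysterectomy or death would fall after her participation had ended.

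**3. Scale, on assumed figures only.**

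- Women affected: 30,000 × 0.001 = 30; 30,000 × 0.01 = 300.
- Deaths: at an assumed 0.02% to 0.05%, 6 to 15 in all. If half follow transfer, 3 to 7.5 are counted.
- An endpoint at 1% in both arms gives 15,000 × 0.01 = 150 events per arm. Missing 10% in each loses 15 per arm and leaves the RR at 1.00.
- Missing 10% under carbetocin and 20% under oxytocin turns a true RR of 1.00 into 0.90 / 0.80 = 1.125. The reverse gives 0.80 / 0.90 = 0.89.
- A true 250 versus 200 events (RR 1.25), missing 20% and 10% respectively, becomes 200 versus 180 (RR 1.11).

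Under-counting can therefore leave the RR unchanged, move it away from 1 or pull it towards 1, depending on shares that the article does not give.

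**The case against.** The strongest reply is that the Study design sentence describes patient flow and never says that recording stops, while the endpoint table and the safety section both say that data run to discharge. The article also condenses a master protocol and a manual of operations, which may deal with transferred women. This stands in part: a reader might infer that the data are lost, but the documents show only that two rules conflict and that one of them, taken literally, would lose the data. It does not remove the point, because the article is not merely silent on a detail. It states a definite end of participation that disagrees with its own endpoint definitions.

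A reader might also infer that the truncation favours carbetocin in the non-inferiority comparison. The documents do not support that. Non-inferiority is tested only on the two primary endpoints, and the Statistics section assesses transfusion, surgery, death and the composite for superiority only. The illustrations above show that the direction of bias is not fixed either.

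Nor do the affected endpoints disappear. Events before transfer, and all events in women never transferred, are still counted. Hysterectomy is not a separate endpoint; it belongs to the surgery endpoint and to the composite. An ICU admission counts in the composite and is recorded as a serious adverse event.

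Finally, the primary endpoints are exposed only narrowly. Transfer must fall within one to two hours of birth, and the woman must first meet the endpoint after it. One who has already lost 500 mL or received an additional uterotonic is already a composite primary event.

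**Conclusion.** The contradiction is real and should be corrected, but its reach is limited. Read literally, the end-of-participation rule truncates secondary and safety data informatively. Those mainly affected are transfusion, surgical procedures, adverse event outcomes and maternal death, the last of which also lacks a stated window. The composite is largely protected for ICU transfers but not for other higher care units. The sample size stands, and so do the formal non-inferiority tests, apart from any transfer within the measurement window.

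The size and direction of any bias cannot be derived from the article. The 30 to 300 women, the 3 to 7.5 counted deaths and the shifted risk ratios all rest on assumed transfer rates, event rates and shares of events after transfer.

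**What to change.** Reconcile Study design with Table 2 and Assessment of safety by separating the end of trial procedures from the end of outcome collection. The text should state that:

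- all endpoints now defined to discharge, maternal death, and the outcomes of adverse and serious adverse events are collected to hospital discharge or death regardless of transfer, from the receiving unit's records;
- primary endpoint status is completed when transfer occurs within the measurement window;
- maternal death as a separate endpoint has the same window.

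This takes a sentence or two in the protocol, a matching line in the manual of operations, and record abstraction for what should be a small number of transferred women. It concerns data collection only and leaves clinical management as it is. Recruitment had begun in five countries with five more to follow, so the wording should be settled before the remaining sites open, and outcomes for women already transferred should be retrieved where records allow.
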